### Statistical analysis

Statistical analyses were conducted using SPSS 20.0 software. Normally distributed data are presented as mean ± standard deviation, with intergroup comparisons performed using one-way analysis of variance (ANOVA) and *post hoc* tests conducted via the Student-Newman-Keuls (SNK) method for Type I error correction. Non-normally distributed data are expressed as median (Q1, Q3), and intergroup comparisons are made using the Kruskal–Wallis test.

For categorical data, counts and percentages are used for intergroup comparisons, employing the *χ*² test with continuity correction or Fisher's exact test as appropriate. The analysis of factors influencing binary outcomes will be performed using binary logistic regression, accounting for potential confounding variables. A *p*-value of <0.05 will be considered statistically significant.

To assess the robustness of the main conclusions of the study, we will conduct the following sensitivity analyses: To control for potential confounding factors as comprehensively as possible, we will include all baseline variables with intergroup differences reaching a significance level of *P* < 0.1 in the univariate analysis, together with the study grouping variable, into the multivariable Logistic regression model. This is to calculate the adjusted odds ratio (aOR) of the effect of DCC + MISA on BPD and its 95% confidence interval (95% CI).

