#### Inclusion criteria

① Infants of 23–29 + 6 weeks gestational age.② Born in Peking University Third Hospital, having spontaneous breathing after birth;③ Diagnosed as NRDS; NRDS is defined as progressive dyspnea that occurs after birth, with or without imaging evidence, excluding other causes of dyspnea.

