### Research grouping

Patients were divided into three groups based on the study's time phases and the differences in treatment they received after birth:

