### Data collection and diagnoses

Demographic data will include gestational age, birth weight, sex, multiple births, antenatal corticosteroid use, mode of delivery, maternal complications, Apgar score, and cord blood gas levels. Clinical data will encompass survival rates, required doses and timing of surfactant administration, blood gas measurements on the first day after birth, need for mechanical ventilation during hospitalization, duration of NCPAP/NIPPV, days on supplemental oxygen, hospitalization costs, and morbidity of BPD, pneumothorax, nasal trauma, pulmonary hemorrhage, hsPDA, IVH, PVL, blood culture-confirmed late onset sepsis, NEC, and ROP.

Pneumothorax will be diagnosed by the presence of air in the pleural cavity in a chest x-ray. Pulmonary hemorrhage will be diagnosed based on the gushing of bloody fluid from the upper airway or endotracheal intubation and when the chest x-ray is consistent with the relevant clinical findings. The diagnosis for hsPDA will be based on clinical signs and echocardiogram. IVH and white matter injury will be diagnosed by cranial ultrasound examination, and IVH will be graded by the Papile classification system. Blood culture-confirmed sepsis will be defined as clinical sepsis with evidence of pathogens in blood culture. NEC will be graded according to the modified Bell's classification system. The diagnosis and staging of ROP will be based on retinal examination by a consultant ophthalmologist.

Pneumothorax will be diagnosed radiographically by detecting air within the pleural cavity on chest radiography. Pulmonary hemorrhage is defined as acute onset of frank blood emanating from the upper airway or endotracheal tube, accompanied by radiographic evidence concordant with clinical manifestations. The diagnosis of hsPDA will be established through integration of clinical indicators and confirmatory echocardiography (13). IVH and PVL will be identified via standardized cranial ultrasonography, with IVH severity classified according to the Papile grading system (14). Culture-confirmed late-onset sepsis requires both compatible clinical signs and isolation of pathogenic microorganisms from blood cultures. NEC will be staged using the modified Bell's classification criteria (15). ROP diagnosis and staging will be determined through comprehensive retinal evaluations performed by a certified ophthalmologist.

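### Continuous secondary outcomes are compared across three non-randomised eras by tests without covariates; adjustment is named only for binary outcomes and BPD

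*Protocol article*

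**What the plan says.** The Statistical analysis section assigns tests by type of data. For normally distributed data, summaries are given "with intergroup comparisons performed using one-way analysis of variance (ANOVA"), followed by SNK post hoc tests. For non-normal data, "intergroup comparisons are made using the Kruskal–Wallis test".

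Adjustment appears twice, both times as logistic regression:
- "The analysis of factors influencing binary outcomes will be performed using binary logistic regression, accounting for potential confounding variables".
- A sensitivity analysis that enters baseline variables differing between groups at P < 0.1. Its stated purpose is narrow: "This is to calculate the adjusted odds ratio (aOR) of the effect of DCC + MISA on BPD".

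The Secondary outcome measures section includes several continuous outcomes: duration of NCPAP/NIPPV, duration of IMV, oxygen days, length of stay, cost, and haemoglobin and haematocrit within 24 h.

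Groups are not randomised: "Patients were divided into three groups based on the study's time phases and the differences in treatment they received after birth". Eligibility covers "Infants of 23–29 + 6 weeks gestational age". The covariates that an adjusted model would need are already on the collection list: "Demographic data will include gestational age, birth weight, sex, multiple births, antenatal corticosteroid use, mode of delivery".

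**The concern.** One-way ANOVA and Kruskal–Wallis have group as their only factor. Between randomised groups that costs little. Here the groups come from 2017–2020, 2021–2024 and 2025–2027, and the eligible range spans seven completed weeks of gestation (23 to 29), so shared eligibility criteria do not guarantee the same mix in each era.

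The group definitions also select differently. Under Research grouping, the DCC+MISA group requires no prenatal contraindication to DCC and a completed 60 s of DCC. Neither ICC group has an equivalent filter.

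If gestational age or birth weight does differ between eras, part of any difference in support days, oxygen days, stay, cost or blood values would reflect case mix and not the strategy. Case mix could create a difference or hide one. The Abstract promises a comparison of short-term efficacy to inform treatment decisions, and these outcomes carry much of it. The plan is also uneven: it recognises that BPD needs adjustment, but names none for IMV days or stay, on which the same baseline factors may act.

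**Working it through.** **Step 1. Methods set against outcomes (protocol article).**

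| Outcome type | Test named | Adjusted model named |
|---|---|---|
| BPD | χ² or Fisher | Logistic, aOR with 95% CI |
| Other binary outcomes | χ² or Fisher | Logistic |
| Support and oxygen days, stay, cost, haemoglobin, haematocrit | ANOVA/SNK or Kruskal–Wallis | None |

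**Step 2. Group sizes.** These come from Sample size calculation and reproduce:
- n₂ = (1.96 + 0.84)² × [0.29 × 0.71/3 + 0.14 × 0.86] / 0.15² = 65.87, so 66, and 3 × 66 = 198.
- With 10% loss, 66/0.9 = 73.3, so 74, and 3 × 74 = 222.

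No figure in the plan is disputed. The sizes used below are 222, 222 and 74.

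**Step 3. Illustration for length of stay, pairwise.** Assumptions, none of them in the document: each week less of gestation adds 7 days of stay; SD of stay is 20, 25 or 30 days; there is no treatment effect; mean gestation in the DCC+MISA era differs by 0.5 week. The spurious difference is 0.5 × 7 = 3.5 days.

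SE = SD × √(1/222 + 1/74); z = 3.5/SE; rejection at two-sided 0.05 = Φ(z − 1.96) + Φ(−z − 1.96).

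| SD | SE | z | Rejection, 74 vs 222 |
|---|---|---|---|
| 20 | 2.68 | 1.30 | 26% |
| 25 | 3.36 | 1.04 | 18% |
| 30 | 4.03 | 0.87 | 14% |

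With a 1-week shift (7 days), z is 2.61, 2.09 and 1.74, and rejection is 74%, 55% and 41%.

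**Step 4. The same for the planned three-group test.** With only the third era shifted by d days, the noncentrality of the omnibus F test is d² × (74 × 444/518)/SD² = d² × 63.43/SD². For d = 3.5 this is 1.94, 1.24 and 0.86 at SD 20, 25 and 30. On 2 and 515 degrees of freedom, rejection is 22%, 15% and 12%. For d = 7 it is 70%, 50% and 36%. The omnibus figures are somewhat below the pairwise ones.

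**Step 5. Does adjustment help?** Simulation with 2,000 replicates per setting, groups of 222/222/74 and no treatment effect. Assumed: correlation between outcome and gestational age of 0.3, 0.5 or 0.7, and a shift of 0.2, 0.3 or 0.5 SD of gestational age in the third era only.

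| Correlation | ANOVA, shift 0.2 to 0.5 SD | Kruskal–Wallis | Linear model adjusted for gestational age |
|---|---|---|---|
| 0.3 | 7–18% | 6–16% | 4–5% |
| 0.5 | 10–39% | 8–38% | about 5% |
| 0.7 | 15–70% | 15–67% | about 5% |

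With no shift, every method gives about 5% (4.1% to 5.0%). The excess comes entirely from the assumed shift, and the adjusted model removes it in this setting.

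**The case against.** The strongest objection is that this rests on silence. The article is condensed, its sentences describe tests by data type without naming the secondary outcomes, and it never says that continuous outcomes will be left unadjusted. An analysis plan that is not shown may add models. That has some force: one cannot say the authors have ruled adjustment out. But the article does more than omit. It names the test for continuous data and, in the same section, says where confounders will be handled. Followed as written, the continuous comparisons are unadjusted.

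A second objection is that the Discussion admits possible bias from differing hospitalisation years, and that baseline data are collected, so a shift would be visible. This stands as mitigation. Seeing an imbalance does not correct for it, however, and the remedies offered (common criteria and a limit on years) do not balance gestational age within the eligible range.

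A reader might infer three stronger things that the document does not support:
- That gestational age did shift between eras. Nothing reports or implies this, and every size above is assumed.
- That any change in case mix would produce a significant result. In the half-week illustration, 74–86% of pairwise comparisons stay non-significant.
- That adjustment would let differences be attributed to the strategy. Era and treatment coincide, so calendar-time effects remain after any covariate adjustment.

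**Conclusion.** The point holds in a conditional form. The plan names tests without covariates for continuous outcomes across three non-randomised eras, and names adjustment only for binary outcomes and BPD. If baseline case mix differs between eras, part of any difference in these secondary outcomes would be case mix.

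The size depends on the shift, the slope on gestation and the SD, none of which the document gives. Under the assumptions shown, a half-week shift raises the chance of a false difference in stay from 5% to roughly 12–26%, depending on the SD and on whether the omnibus or the pairwise test is used. With no shift there is no inflation.

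Only secondary outcomes are affected; the BPD analysis and the sample size are not touched. It should be changed because the covariates are already collected, but it does not threaten the primary result.

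**What to change.** For each continuous secondary outcome, report an adjusted DCC+MISA versus ICC+MISA difference with 95% CI from a regression on group and prespecified baseline covariates. These should include at least gestational age, with birth weight, sex, multiple birth and antenatal steroids.

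- **Haemoglobin and haematocrit:** linear regression.
- **Support and oxygen durations, stay, cost:** a model suited to skewed data that allows zeros, for example a GLM with log link.
- **IMV days:** a negative binomial or two-part model. Many MISA infants may have no IMV days, so a log-transformed outcome would be undefined and median regression could degenerate.

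Keep ANOVA and Kruskal–Wallis as descriptive. State two limits: deaths cut durations and stay short, and calendar-time confounding remains because era and treatment coincide.

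The cost is some plan wording, a few extra models and some dependence on model form. No new data or infants are needed.

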### Sample size calculation

Our hospital has previously conducted a prospective multicenter clinical study comparing MISA and tracheal intubation in the early stages. The results indicated that the incidence of BPD in premature infants with a gestational age of less than 30 weeks was 29% in the MISA group (*n* = 31) and 70% in the tracheal intubation group (*n* = 20). Assuming the BPD incidence rate (p_1_) in the ICC + MISA group for this study is 29%, and the incidence in the DCC + MISA group (p_2_) decreases by 15%–14%, we will set the Type I error (α) at 0.05 and the Type II error (β) at 0.2. With a sample size ratio (k) of 3:1 between the DCC + MISA and ICC + MISA groups, the sample size calculation formula is:$$n_{2}=\frac{{\left(z_{1-a/2}+z_{1-\beta }\right)}^{2}[\;p_{1}(1-p_{1})/k+p_{2}(1-p_{2})]}{{\left(\;p_{1}-p_{2}\right)}^{2}}$$*n*_1_ = *k* × *n*_2_.

Where z_(1−*α*/2)_ = 1.96 and _z(1−*β*)_ = 0.84.

This results in a sample size of 66 for the DCC + MISA group and 198 for the ICC + MISA group. Assuming a 10% loss to follow-up, the adjusted sample sizes will be 74 for the DCC + MISA group and 222 for the ICC + MISA group. Additionally, the sample size for the ICC + tracheal intubation group is also set at 222 cases.

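### The analysis section does not make DCC+MISA versus ICC+MISA, the pair the study is sized on, the primary test; a three-group test of BPD would not answer the DCC question

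*Protocol article*

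**What the plan says.** The Sample size calculation section of the protocol article builds the study on two groups. It begins "Assuming the BPD incidence rate (p_1_) in the ICC + MISA group for this study is 29%, and the incidence in the DCC + MISA group" and takes the latter to be 15 points lower, at 14%. It adds: "we will set the Type I error (α) at 0.05 and the Type II error (β) at 0.2". The intubation group plays no part in the formula; its size is simply set to 222. The same section reports that BPD in the hospital's previous multicentre study "was 29% in the MISA group (*n* = 31) and 70% in the tracheal intubation group (*n* = 20").

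The Statistical analysis section describes comparisons among three groups:

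- **Normally distributed data:** ANOVA, followed by Student-Newman-Keuls pairwise tests.
- **Skewed data:** "Non-normally distributed data are expressed as median (Q1, Q3), and intergroup comparisons are made using the Kruskal–Wallis test". No pairwise step follows.
- **Categorical data:** "For categorical data, counts and percentages are used for intergroup comparisons, employing the *χ*² test with continuity correction or Fisher's exact test as appropriate". No pair and no follow-up test are named. BPD and survival, the primary outcomes, fall here.
- **Logistic regression:** planned in general terms for factors influencing binary outcomes. An adjusted odds ratio for the effect of DCC+MISA on BPD, with a 95% CI, is listed under sensitivity analyses. The reference group is not given.

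The only significance rule is p below 0.05.

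**The concern.** A three-group χ² or Kruskal–Wallis test has the null hypothesis that all three groups are equal. The study was sized to ask whether DCC+MISA differs from ICC+MISA. These are different questions. On the protocol's own planning figures, the three-group null for BPD is already false because of the 2017–2020 intubation cohort, whatever DCC does.

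The Conclusion section frames success as DCC+MISA doing better than the ICC+MISA or the ICC+intubation group. With no primary pair named, an overall P<0.05 driven by the oldest cohort could be taken as support for DCC. The text does not settle which test is meant: the continuity correction points to 2×2 tables, but no such table is specified.

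**Working it through.** **Inputs** (Sample size calculation section): p1 = 0.29 (ICC+MISA), p2 = 0.14 (DCC+MISA), k = 3, z-values 1.96 and 0.84, 10% loss, intubation BPD rate 0.70 from 20 infants.

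**Step 1: reproduce the plan's figure.**

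n2 = (1.96 + 0.84)² × [0.29×0.71/3 + 0.14×0.86] / 0.15² = 65.87, so 66. Then n1 = 3 × 66 = 198; 66/0.9 = 73.3, so 74; and 3 × 74 = 222. All stated sizes reproduce, so the sizing is a two-group calculation for DCC+MISA versus ICC+MISA.

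**Step 2: the three-group χ² for BPD when DCC does nothing.** Set both MISA groups to 29% and intubation to 70%, with 198 intubation, 198 ICC+MISA and 66 DCC+MISA (the intubation group taken as 198 to match ICC+MISA before loss).

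- Pooled rate: (198×0.70 + 264×0.29)/462 = 215.16/462 = 0.4657.
- Noncentrality: [198×(0.70 − 0.4657)² + 264×(0.29 − 0.4657)²] / (0.4657×0.5343) = 19.02/0.2488 = 76.4.
- On 2 df at alpha 0.05 (critical value 5.99), the probability of P<0.05 is over 0.999. At 222/222/74 the noncentrality is 85.7, with the same result.

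**Step 3: does it depend on the 70%?** That rate is 14/20, with an exact 95% CI of 45.7% to 88.1%. Simulated probability of overall P<0.05 (100,000 runs per setting), with both MISA groups at 29%:

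| Intubation BPD rate | 198/198/66 | 222/222/74 |
|---|---|---|
| 29% | 0.05 | 0.05 |
| 35% | 0.21 | 0.23 |
| 40% | 0.59 | 0.65 |
| 45% | 0.90 | 0.93 |
| 50% | 0.99 | 0.995 |
| 70% | >0.999 | >0.999 |

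The lower confidence limit lies just above the 45% row, so the probability there is about 0.9 or more.

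**Step 4: does the overall test separate benefit from harm?** With intubation at 70% and ICC+MISA at 29%, it rejects in about 100% of simulated trials whether DCC+MISA is 14%, 29% or 40%.

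**Step 5: the direct contrast.** In the no-effect scenario at 70%, a two-group χ² of DCC+MISA against ICC+MISA (66/198) rejects in 5.0% of runs, or 3.4% with continuity correction. Requiring the overall test to be significant first also gives 5.0%.

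**Step 6: other outcomes.** The document gives no survival rates. Assumed survival of intubation versus both MISA groups, at 198/198/66, gives these overall rejection rates: 93% v 95%, 0.10; 88% v 92%, 0.22; 90% v 95%, 0.42; 85% v 95%, 0.92. For Kruskal–Wallis, an assumed lognormal outcome (log-SD 1) with only the intubation group shifted by 0.2, 0.3 or 0.5 gives 44%, 80% and 99.7%. These are illustrations and do not come from the plan.

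**The case against.** The strongest reply is that a three-group test of BPD is never stated. Continuity correction is a 2×2 device, so the sentence may mean pairwise tables. The comparison of interest is clear from the Sample size calculation and Conclusion sections, the logistic model yields a DCC+MISA estimate, and follow-up tests and reference categories are often left to a full analysis plan.

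Much of this stands. The text is ambiguous rather than plainly wrong, and if all three groups enter the logistic model with ICC+MISA as reference, its odds ratio is the contrast needed. But against intubation, or against the two ICC groups pooled, it would mix the effect of MISA with that of DCC, and the document does not say which is meant. Nor is this only condensation: the article names a pairwise method for one data type and none for the type that holds the primary outcomes.

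Three stronger readings are tempting and not supported:

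- **That significance is near-certain for survival and skewed outcomes too.** No rates are given, and modest assumed survival gaps give far lower probabilities.
- **That the 5% error rate is inflated.** If intubation truly differs, rejecting equality of all three groups is correct. The result misleads only if it is read as evidence about DCC.
- **That the plan contains no DCC-specific estimate.** It has one for BPD, as a sensitivity analysis.

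**Conclusion.** The point holds as a mismatch between sizing and analysis. The study is sized on DCC+MISA versus ICC+MISA for BPD, and the analysis section does not make that pair the primary test or fix a reference group.

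The size is conditional. If BPD is tested across three groups, and the MISA and intubation rates are near the planning values, the overall test is significant almost surely whatever DCC does. This survives the lower confidence limit of the intubation rate but weakens below it (0.59 at 40%). If pairwise 2×2 tests are intended, that consequence does not arise, but the pair still has to be named. For survival and skewed outcomes the gap is structural and cannot be quantified from the document.

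**What to change.** In the Statistical analysis section:

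1. Name DCC+MISA versus ICC+MISA for BPD as the primary contrast at two-sided 0.05, reported as a risk difference or odds ratio with 95% CI. State whether the continuity correction is used.
2. Set ICC+MISA as the reference category of the grouping variable in the logistic model.
3. Use the same contrast for survival and the other categorical outcomes.
4. Add multiplicity-adjusted pairwise tests after Kruskal–Wallis, for example Dunn's test with Holm adjustment.
5. State that an overall three-group P-value alone supports no claim about DCC, and treat comparisons with the intubation group as secondary.

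This is wording only, with no extra infants or data, and can be done while the prospective cohort (planned to October 2027) is running. The cost is that the primary P-value will be less favourable than the overall three-group one.

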#### DCC+MISA group

From Aug. 31, 2025 to Oct. 31, 2027. Infants without contraindications to DCC, as determined by prenatal evaluation, receive immediate non-invasive respiratory support after birth. DCC is successfully performed for 60 s, followed by a diagnosis of NRDS. A therapeutic dose of PS is administered via MISA within the first 2 h after birth.

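### The primary BPD comparison is not identified as adjusted, and the one adjusted effect specified is a sensitivity analysis whose covariates are chosen by a between-group P < 0.1 screen

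*Protocol article*

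**What the plan says.** All of the analysis text is in the protocol article, Statistical analysis.

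- **Crude comparison.** "For categorical data, counts and percentages are used for intergroup comparisons, employing the" chi-square test with continuity correction, or Fisher's exact test. BPD and survival at 36 weeks are categorical, so this sentence covers them.
- **General regression sentence.** "The analysis of factors influencing binary outcomes will be performed using binary logistic regression, accounting for potential confounding variables". It names no covariates and is not labelled primary.
- **Adjusted group effect.** This comes in the next paragraph, which opens: "To assess the robustness of the main conclusions of the study, we will conduct the following sensitivity analyses". There, "we will include all baseline variables with intergroup differences reaching a significance level of" P < 0.1 in univariate analysis, together with the grouping variable, in a multivariable logistic model. The purpose is given: "This is to calculate the adjusted odds ratio (aOR) of the effect of DCC + MISA on BPD", with a 95% confidence interval.

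The candidate variables appear under Data collection and diagnoses. The demographic list starts with gestational age, birth weight, sex and multiple births, and continues with "antenatal corticosteroid use, mode of delivery, maternal complications, Apgar score, and cord blood gas levels". Baseline is not defined in either section.

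Under Research grouping, the cord is clamped within 20 s in both ICC groups. In the third group, "DCC is successfully performed for 60 s, followed by a diagnosis of NRDS". The groups cover 2017–2020, 2021–2024 and August 2025–October 2027, so they do not overlap in time.

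**The concern.** The groups are not randomised and not concurrent, and the Discussion concedes possible bias from differences in hospitalisation years and treatment approaches. In such a design the adjusted estimate should be the one that is interpreted. Here the fully specified adjusted estimate serves to check conclusions already reached by other means.

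The covariate rule adds two problems.

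1. It selects on the p-value of the imbalance. Confounding depends on the size of the imbalance and on how strongly the variable predicts BPD. The p-value reflects the imbalance and the sample size, and says nothing about prognosis. With one group of 74, a strong predictor with a moderate imbalance can be left out, while a trivial predictor with a chance difference is let in.
2. It sets no limit on timing. Apgar score and cord blood gas are recorded at or after clamping. If DCC changes them, they will tend to differ between groups, pass the screen, and absorb part of the effect under study.

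At stake are the BPD estimate that readers will take from the study and whether its adjusted version is fixed before the data are seen.

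**Working it through.** **1. The plan's own figure.** Inputs from Sample size calculation: p1 = 0.29, p2 = 0.14, k = 3, z values 1.96 and 0.84.

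n2 = (1.96 + 0.84)² × [0.29 × 0.71/3 + 0.14 × 0.86] / 0.15² = 7.84 × (0.06863 + 0.12040) / 0.0225 = 65.87, rounded up to 66; 3 × 66 = 198.

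Allowing for 10% loss: 66/0.9 = 73.3, so 74; 3 × 74 = 222. Both stated pairs reproduce. The formula is an unadjusted comparison of two proportions, which fits the reading that the crude comparison drives the design.

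**2. Chance that a gestational-age imbalance passes the screen.** Group sizes 222 and 74 are from the protocol; the imbalance d (in SD units) is assumed.

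SE = √(1/222 + 1/74) = 0.1342; z = d/SE; P(pass) = Φ(z − 1.645) + Φ(−z − 1.645).

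| d (SD) | z | pass, two groups | pass, three-group ANOVA |
|---|---|---|---|
| 0.2 | 1.49 | 44% | 39% |
| 0.3 | 2.24 | 72% | 68% |
| 0.4 | 2.98 | 91% | 89% |
| 0.5 | 3.73 | 98% | 98% |

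The last column uses the noncentral F distribution with groups 222/222/74 and only the DCC+MISA mean shifted.

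For a binary covariate (assumed 50% v 60%), the pass rate is 41% at 66 v 198 and 45% at 74 v 222. For 50% v 55% it is 17% and 19%.

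**3. What an omitted confounder can do to the crude test.** Assume no true DCC effect and 66 v 198 infants. A binary confounder is present in 50% of ICC+MISA and a fraction c of DCC+MISA, and multiplies BPD risk by RR. The baseline risk is set so that ICC+MISA stays at 29%: r0 = 0.29/(0.5 RR + 0.5). The apparent DCC+MISA rate is r0 × (c RR + 1 − c).

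| c | RR | apparent DCC+MISA rate | spurious difference | two-sided error of nominal 5% test | covariate passes screen |
|---|---|---|---|---|---|
| 40% | 2 | 27.1% | 1.9 points | 5.8% | 41% |
| 40% | 3 | 26.1% | 2.9 points | 7.0% | 41% |
| 30% | 2 | 25.1% | 3.9 points | 8.7% | 90% |
| 30% | 3 | 23.2% | 5.8 points | 14.0% | 90% |

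The planned effect is 15 points. The last column matters: where the bias is largest, the screen would usually let the covariate into the sensitivity model. The crude test carries the bias in every row.

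**4. Timing of candidate covariates.** The exposure is clamping within 20 s v at 60 s. Gestational age, birth weight, sex, multiple birth, antenatal corticosteroids and mode of delivery are settled before or independently of clamping. An Apgar score at one minute or later and a cord blood sample follow or overlap it. The Discussion says that immediate clamping can reduce venous return and cardiac output, so an effect on both variables is plausible on the protocol's own mechanism.

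**5. Room for a fixed model.** Expected BPD events in the two groups: 0.14 × 66 + 0.29 × 198 = 9.2 + 57.4 = 66.7, about 67. For six covariates and the group term, that is about 9.5 events per term if each takes one parameter.

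**The case against.** Several stronger readings are tempting and are not supported.

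- **That confounding is handled only in a sensitivity analysis.** The sentence on binary logistic regression stands outside the sensitivity paragraph and refers to potential confounders. An article may leave its covariate list to the full protocol. This stands. What remains is that the sentence does not identify the primary BPD comparison as adjusted, and that the one adjusted group effect spelled out has sensitivity status.
- **That chi-square is the declared primary test.** No test is named primary, and the chi-square sentence covers all categorical data. A reader may infer that the crude comparison carries the main conclusion from the robustness wording and the unadjusted sample size. It is a fair inference, not a statement in the protocol.
- **That Apgar score and cord gas are consequences of DCC.** The protocol does not say so. They may also reflect the infant's condition before clamping, and the list of demographic data is not expressly equated with baseline variables. The supportable claim is that the rule may admit variables that DCC may affect.
- **That the screen generally drops important confounders.** It tends to miss small imbalances and keep large ones, as the pass rates above show.
- **That ignoring sibling correlation is an error.** The article is silent on clustering, which is commonly left to the analysis plan. With an assumed 30% of infants in twin pairs and correlation 0.2–0.5, the design effect is 1 + 0.3 × 0.2 = 1.06 to 1 + 0.3 × 0.5 = 1.15, and a nominal 5% test runs at 5.7–6.8%. This is minor.
- **That adjustment would remove the confounding.** Group and calendar period coincide, so no covariate list separates them. This stands in full, but it does not justify a data-driven list for the confounders that were measured.

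**Conclusion.** The point holds in this form: in a non-concurrent comparison, the protocol does not identify the primary BPD analysis as adjusted, and it gives the only specified adjusted effect of DCC+MISA a supporting role with a poor covariate rule. Because the P < 0.1 rule is stated, this is a method to replace and not a detail left out.

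The sizes rest on assumed imbalances, since the protocol gives none. Under the assumed confounding, the crude test would show a spurious benefit of about 2 to 6 points and reject a true null about 6–14% of the time. The screen's weakness is confined to small and moderate imbalances: 56% are missed at 0.2 SD, 28% at 0.3 SD and 9% at 0.4 SD. The possible entry of Apgar score and cord gas rests on timing, on the protocol's mechanism and on the undefined term baseline; its effect on the estimate cannot be quantified from the document.

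**What to change.** Name the primary BPD analysis as one logistic model of DCC+MISA v ICC+MISA with a fixed set of pre-exposure covariates already in the data list: gestational age, birth weight, sex, multiple birth, antenatal corticosteroids and mode of delivery. Drop the P < 0.1 screen. Leave Apgar score and cord blood gas out of the model. Report the adjusted odds ratio with its 95% confidence interval as the main result and keep the crude chi-square as supportive.

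Standard errors clustered on mother are an optional minor addition.

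State plainly that residual confounding by era remains after adjustment.

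The cost is a change of wording and a few degrees of freedom, against about 67 expected events under the planning rates. No new data are needed. The change should be made before outcomes in the prospective group are known.
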